**PROTOCOL SYNOPSIS**

**TITLE:**

A randomized controlled trial of acupuncture for residual insomnia associated with major depressive disorder

**OBJECTIVE:**

To evaluate the efficacy and safety of acupuncture treatment for residual insomnia and other residual symptoms associated with major depressive disorder

**TRIAL DESIGN:**

Randomized controlled trial

**TRIAL POPULATION:**

This trial will recruit 96 subjects who fulfill the inclusion/ exclusion criteria.

**CLINICAL EFFICACY VARIABLES:**

Primary outcomes measures are sleep parameters measured by actigraphy, Insomnia Severity Index (ISI) and sleep log, and depressive state as measured by Hamilton Depression Rating Scale (HDRS). Secondary outcomes are Pittsburgh Sleep Quality Index (PSQI) and Sheehan Disability Index (SDI).

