The subjects will receive the Structured Clinical Interview for DSM-IV to evaluate psychiatric diagnoses and polysomnography to exclude specific sleep disorders prior to randomization. Block randomization is used in the randomization procedure. This is performed by using Excel to generate a randomized block list.16 Subjects are randomly assigned to one of the three groups after baseline visit.

Method of blinding

The subjects are told as follows “This study is to evaluate the therapeutic effects of acupuncture on treating insomnia in depressive patients. You will be randomly assigned to traditional acupuncture group for insomnia or acupuncture-like placebo treatment group”; “Traditional acupuncture is an acupuncture treatment that conventionally used in Chinese medicine practice; placebo acupuncture is a procedure which mimics the real acupuncture procedure and give you a perception that you are receiving the acupuncture treatment”. The researchers who analyse the data will be blind to the treatment allocation.

Concomitant Therapy

Antidepressants will be maintained the same dosage during the study period. Sedatives, hypnotics or anxiolytics are allowed during the study. The subjects are told to record their dosage of these medications. Drug counts will be conducted at each study visit. Individual psychotherapy should be maintained if it is ongoing prior to the study. Any new form of therapy or education is disallowed.

*Outcome Assessment*

Subjective assessment

1. Insomnia Severity Index (ISI) (Primary outcome measure)

ISI is a 7-item self-rating scale. The subjects rate their severity of sleep problem and the daytime function performance due to insomnia using a 5-point Likert scale.

2. Sleep log

The subjects record their daily sleep-wake schedule on a standardized sleep log.

3. Hamilton Depression Rating Scale (HDRS)

HDRS is a 21-item scale which the clinicians used to rate the severity of patients’ depression. HDRS rates the severity of other depressive symptoms such as low mood, insomnia, agitation, anxiety and weight-loss.

4. Pittsburgh Sleep Quality Index (PSQI)

PSQI is a self-rating scale that assesses the subjects’ sleep in the past month. It has seven components, namely subjective sleep quality, sleep latency, sleep duration, habitual sleep efficiency, sleep disturbance, use of sleeping medication, and daytime dysfunction.

5 Sheehan Disability Index (SDI)

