SDI is a 3-item self-rating scale that assesses the subjects’ functioning regarding work/study, social life and family.

Objective assessment

Actigraph

Actigraph is a watch-like device used to estimate sleep-wake schedules by measurement of activity. The subjects are asked to wear the actigraph on the dominant wrists prior to light off for 3 consecutive nights. Subjects will be told to have usual bedtime when they are measured by actigraph.

Assessment for safety

Reason for withdrawal

When a subject withdraws before completing the study, the reason for withdrawal will be recorded.

Adverse events

Adverse events will be assessed at each visit. The researcher will ask using open-ended questions whether the subjects experience any adverse events during the assessment visit.

Assessment for credibility

Credibility of treatment rating scale (modified by C Vincent) will be used to assess the credibility of the treatments.17 The 4-item scale is specially designed to assess the credibility of acupuncture.

*Data Analysis*

Sample size estimation

Insomnia Severity Index (ISI) is selected as the primary outcome measure. The sample size estimation is based on our pilot study. We found that the SD of ISI score in the treatment and control group was 4.7 and 3.6, respectively, while the baseline and endpoint ISI score correlation coefficient was roughly 0.5. Vickers and Altman proposed that analysis of covariance (ANCOVA) was the preferred approach to analyse controlled trials with baseline and follow up measurements.18 We estimate the sample size requirement per treatment group using:

(1- ρ2)

An adjustment factor (1- ρ2) is used to determine the sample size in each group;19 and ρ is the baseline and endpoint measure correlation coefficient.

Let type I error a = 0.05; type II error β = 0.20; and power (1-β) = 80%. The SD δ1= 4.7, δ2 = 3.6 and ρ = 0.5. A clinically significant treatment effect is taken as a 3 ISI point between-group difference (Δ = 3). Therefore, a sample size of 23 is needed in each group. We estimate a 20% attrition rate; hence a sample size of around 30 in each group (90 in total) is planned for this study.

Data Management and Analysis

All data are double-entered and checked for consistency prior to analysis.

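### The synopsis names at least four primary outcomes; the body names ISI alone and sizes the trial for one ISI comparison

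*Protocol*

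**What the plan says.** The protocol defines the primary outcome in three places.

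- **Synopsis, Clinical Efficacy Variables:** "Primary outcomes measures are sleep parameters measured by actigraphy, Insomnia Severity Index (ISI) and sleep log, and depressive state", with depressive state measured by HDRS. The next sentence leaves only two instruments on the secondary side: "Secondary outcomes are Pittsburgh Sleep Quality Index (PSQI) and Sheehan Disability Index (SDI").
- **Plan of Investigation, Outcome Assessment:** the first entry reads "Insomnia Severity Index (ISI) (Primary outcome measure"). Sleep log, HDRS, PSQI, SDI and actigraphy follow without that label.
- **Plan of Investigation, Sample size estimation:** "Insomnia Severity Index (ISI) is selected as the primary outcome measure". The error rates ("Let type I error a = 0.05; type II error β = 0.20; and power (1-β) = 80"%) appear only here, in the ISI calculation.

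The Data Management and Analysis section gives a time × group ANCOVA with the baseline value as covariate. It does not say which outcome or visit is decisive. Table 1 schedules ISI at four visits after baseline.

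**The concern.** Sleep log, HDRS and actigraphy are primary in one part of the current text and not in another. The four-outcome list cannot simply be dismissed as a slip. The synopsis objective covers residual symptoms beyond insomnia, which suits HDRS as a primary outcome. The Introduction gives the use of an objective measure as a reason for the larger study, which suits actigraphy. The Aims section is narrower and speaks of residual insomnia only. Someone reporting the trial could cite the protocol for either definition.

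At stake is which hypothesis the trial confirms. With two definitions available, the choice could be made after the results are known. The type I error and power that the protocol states belong to only one of the two.

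**Working it through.** **Inputs.** From Sample size estimation: "The SD δ1= 4.7, δ2 = 3.6 and ρ = 0.5"; Δ = 3 ISI points; α = 0.05; power 80%; 20% attrition. From the synopsis: four primary measures, counting actigraphy and sleep log once each. The protocol gives no correlation between outcomes, so those below are assumed.

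**Step 1: reproduce the stated sample size.** The two-group formula with the protocol's (1 − ρ²) factor is

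n = (SD₁² + SD₂²)(z₀.₉₇₅ + z₀.₈₀)² / Δ² × (1 − ρ²)

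- SD₁² + SD₂² = 22.09 + 12.96 = 35.05
- (1.960 + 0.842)² = 7.849
- 35.05 × 7.849 / 9 = 30.57
- 30.57 × (1 − 0.25) = 22.93, rounded up to 23

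This matches "Therefore, a sample size of 23 is needed in each group". The protocol does not state sidedness; a one-sided test would give 19, so the calculation is two-sided. Attrition: 23 / 0.8 = 28.75, or 29, consistent with the planned figure of about 30. The size therefore rests on one ISI contrast at the full 0.05.

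**Step 2: type I error if any one of four outcomes at 0.05 were enough.** Under independence it is 1 − 0.95⁴ = 18.5%, and it can never exceed 4 × 0.05 = 20%. For correlated outcomes, one million sets of four equally correlated two-sided z-tests were simulated:

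| Assumed correlation | Family-wise error |
|---|---|
| 0 | 18.5% |
| 0.3 | 17.3% |
| 0.5 | 15.6% |
| 0.7 | 13.0% |
| 0.9 | 9.4% |

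**Step 3: type I error under the other readings.** If all four outcomes had to succeed, the error would be at most 5%, and power could not exceed that of ISI alone. With ISI as sole primary and one prespecified test, the error is 5%.

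**Step 4: power if four primaries were kept with Bonferroni.** Each test has α = 0.05 / 4 = 0.0125, with z₀.₉₉₃₇₅ = 2.498.

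- Standard error at 23 per group: √(35.05 × 0.75 / 23) = 1.069
- 3 / 1.069 = 2.806
- Power: Φ(2.806 − 2.498) = 62%, against 80% at 0.05
- With 24 evaluable per group (30 × 0.8), power is 64%
- For 80% power: 35.05 × (2.498 + 0.842)² / 9 × 0.75 = 32.6, or 33 evaluable; 33 / 0.8 = 41.25, or 42 randomised per group

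These figures are for ISI. None can be computed for actigraphy, sleep log or HDRS, because the protocol gives no SD or target difference for them.

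**The case against.** The strongest reply is that the body is clear and consistent. It labels ISI primary, selects it again for the sample size, and the stated number follows. On that reading the synopsis is loosely worded, one prespecified ISI test keeps 5%, and power for ISI alone is all that is needed. A multiplicity rule could also sit in a statistical analysis plan that is not at hand. This limits the consequence but does not remove the contradiction: an analysis plan has to take its primary outcome from the protocol, and this protocol supplies two definitions.

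A reader might infer more than the documents support:

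- **That the 5% error rate fails.** This needs the synopsis to govern, any single outcome to suffice, and no adjustment to be made. The protocol states no such success rule.
- **That the error is several times 0.05.** At the lower end of the range it is about twice 0.05. Independence is also unlikely, since the protocol itself lists insomnia among the symptoms that HDRS rates.
- **That counting more tests shows a larger figure.** The protocol does not list the actigraphy parameters; SOL, WASO and SE are named only for the sleep diary. Nor does it say that each pairwise contrast between arms decides success. Totals built on those counts rest on assumptions from outside the text.
- **That every primary could be claimed at any of four visits.** Table 1 has no actigraphy at the visit after two weeks of treatment, so actigraphy has three visits after baseline.

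**Conclusion.** The contradiction is established from the text and must be resolved, because it decides what the trial can confirm. The design supports only the ISI definition: 23 per group reproduces for one two-sided ISI comparison at 0.05, and the stated power applies to nothing else.

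The effect on the error rate is conditional. It would be about 9% to 19% if any one of four outcomes could carry the claim at 0.05 unadjusted, with assumed common correlations from 0.9 to 0 and each instrument counted once. Under the body's definition with one prespecified test it stays at 5%.

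**What to change.** Change the synopsis so that ISI is the sole primary outcome, and list actigraphy, sleep log and HDRS with PSQI and SDI as secondary. In the same edit, name one visit for the primary ISI comparison, before the waiting-list group starts treatment. Under Study Design that group is treated after 8 weeks, so D113 falls after the changeover and D57 falls at about that time. The 1-week posttreatment visit (D29) is one suitable choice, as the first scheduled visit after all nine sessions. The protocol does not dictate it.

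The cost is synopsis wording. No new data are needed, and the sample size stays at 23 evaluable per group. The sponsor gives up claiming success on a non-ISI outcome.

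If the sponsor prefers several primaries, the protocol must say whether one or all must succeed, how alpha is handled, and what power each has. With Bonferroni over four outcomes, restoring 80% power for ISI takes 42 randomised per group, or 3 × 42 = 126 in total against the 90 in the sample size section.

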**Introduction**

Major depressive disorder (MDD) is a debilitating illness that affects an estimated 13% of the general population.1 It was the fourth leading cause of disability and disease, accounting for 4.4% of the total disability-adjusted life years in the year 2000.2 Residual symptoms in MDD can be defined as core depressive symptoms that have not resolved with treatment.3 Insomnia is one of the most common residual symptoms associated with MDD.

Previous studies have shown that residual symptoms associated with MDD are common. Approximately one third of patients with MDD fail to fully respond to antidepressant treatment of adequate dose and duration.4 In one study, Nierenberg et al. investigated 108 depressed patients who had received an 8-week treatment of fluoxetine, an antidepressant.5 They found that the prevalence of residual insomnia was 44%, followed by fatigue (38%) and diminished interest (27%). Nelson et al. showed that the prevalence of different subtypes of residual insomnia was: difficulty initiating asleep (37%), midnight awakening (33%), and early morning awakening (20%).6

Effective treatment of residual symptoms is essential, since their persistence correlates with a greater risk of MDD recurrence and relapse as well as worse psychosocial functioning. Tranter et al. found that depressed patients with residual symptoms had a relapse rate 3-6 times higher than in those who experienced full remission.7 In another study, Mojtabai et al. found that the severity of residual symptoms was associated with the number of days of impaired occupational functioning.8

Residual insomnia can be a symptom of MDD that requires longer time to remit, a side effect of pharmacological treatment, or a feature etiologically different from but coexist with MDD.3 In a study that compared the rate of residual insomnia following pharmacotherapy or cognitive behavioral therapy for MDD. Carney et al. found that the rate of residual insomnia after drug and non-drug treatment was 53% and 50%, respectively, suggesting that medications alone cannot account for the residual insomnia symptoms.9

There have been limited studies examining the treatment of residual insomnia in MDD. One approach is to treat residual insomnia by augmentation of antidepressant treatment using drug and non-drug approaches. On the other hand, pharmacological or psychological treatments targeting insomnia symptoms may enhance the recovery of both sleep and mood disturbance.

Medications that are used to treat insomnia are limited by adverse effects, abuse and dependence. Psychological treatments are time intensive and require significant training for effective implementation. Pharmacological and psychological treatments of MDD have similar limitations. Acupuncture is one of the safest complementary therapies and has been used to treat insomnia and depression.10,11 Our previous randomized placebo-controlled study has shown that electroacupuncture is effective for primary insomnia.12

We aim to extend the use of acupuncture for treating residual insomnia associated with MDD. The reason for choosing this patient population is that the currently available pharmacological and psychological treatments have their limitations and may not be effective. In addition, the outcome and functioning of partially remitted depressed patients would be enhanced with remission of the residual symptoms.

We have conducted a pilot study comparing the efficacy of electroacupuncture, minimal acupuncture and placebo acupuncture for the treatment of residual insomnia in 30 subjects with MDD. We found that the subjects in electroacupuncture and minimal acupuncture groups had significantly greater improvement in Insomnia Severity Index (ISI) and Pittsburgh Sleep Quality Index (PSQI) scores at 4-week posttreatment than those in placebo acupuncture group (ANCOVA, ISI: F = 5.33, p = 0.01; PSQI: F = 7.93, p = 0.002). In view of the initial positive findings, it is important to extend the study for a longer follow-up period, in a larger sample and using objective outcome measure.

**Aims**

To evaluate efficacy and safety of electroacupuncture for residual insomnia associated with MDD.

**Plan of Investigation**

*Study Design*

The proposed study is a randomized, prospective, placebo-controlled, single-blind trial of electroacupuncture for residual insomnia associated with MDD. The study design aims to differentiate three plausible mechanisms for sleep improvement in patients with insomnia symptoms: (1) needling at specific sites based on traditional Chinese medicine (TCM) theory; (2) characteristic and incidental elements of acupuncture treatment, e.g. credibility of intervention, patient expectations;13 and (3) underlying fluctuations in the disorder, regression to the mean, or non-specific improvement associated with participating in a clinical trial.

Eligible patients will be randomized in a ratio of 1:1:1 to: (1) traditional electroacupuncture; (2) placebo acupuncture using Streitberger needle; and (3) waiting list control group. Active or placebo acupuncture treatment will be given 3 sessions per week for 3 weeks. Patients in the waiting list control group will not receive any treatment for a period of 8 weeks after randomization. After that time, they will receive the same treatment as in the traditional electroacupuncture group. The subjects’ sleep and residual symptoms will be assessed at baseline, after completing 2 weeks of acupuncture treatment, and at 1-week, 5-week and 13-week posttreatment.

*Subjects*

Outpatients, aged from 18 to 65 years, with a previous DSM-IV MDD and a chief complaint of insomnia will be invited to participate in this study. Written informed consent would be obtained prior to study procedure. Subjects would be excluded if they: (1) have a Hamilton Depression Rating Scale scores above 18; (2) have sleep apnea or periodic limbs movement disorder detected by overnight polysomnography; (3) have suicidal risk; (4) have previous history of schizophrenia, other psychotic disorders, and bipolar disorder; (5) are pregnant, breast-feeding, or woman of childbearing potential not using adequate contraception; (6) have infection or abscess close to the site of selected acupoints and in the investigator’s opinion inclusion is unsafe; and (7) are taking Chinese herbal medicine or over-the-counter drugs which are intending for insomnia.

The number of subjects to be recruited in each treatment group would be 30.

*Treatment Protocol*

Traditional Acupuncture

Patients will be treated at bilateral Ear Shenmen (神門), Ear point Heart (心), Sishencong EX-HN1 (四神聰), Anmian (安眠), and unilateral Yingtong EX-HN3 (印堂) and Baihui DU20 (百會). The acupoints are empirical for treating insomnia in term of TCM theory and have been used in our previous study of acupuncture for primary insomnia.

Skin around these points will be sterilized by 75% alcohol and then sterilized disposable needle is inserted to each point by a registered Chinese medicine practitioner. “De qi”(an irradiating feeling considered to be indicative of effective needling) is achieved if possible. An electric-stimulator (CEFAR Acus II, Lund, Sweden) is connected to these needles to give an electric-stimulation in continuous wave, frequency of 4 Hz, 0.45 ms square wave pulses and constant current. Surgical tape or hair pin will be adhered to the needles. It is to increase the similarity between treatment and control group which will be described later. The needles will be left for 30 min and then removed. Acupuncture treatment will consist of three sessions per week for 3 consecutive weeks.

Placebo Acupuncture

The sterilization procedure is the same as the acupuncture group for insomnia. Placebo needles designed by Streitberger will be used.15 The placebo needles are blunt needle that will not penetrate the skin during needle insertion. The handles of these placebo needles will slide over the needle when it is compressed, giving it the appearance of penetrating the skin. The placebo needles are inserted to the site 1 inch beside the acupoints in order to avoid the acupressure effect. The needles are held by a surgical tape or hair pin in hairy region to imitate the retention of needles. The needles are connected to an electric-stimulator with zero frequency and amplitude. The number, duration and frequency of the treatment sessions, and the intervention procedure will be the same for traditional acupuncture and placebo acupuncture. To ensure standardization of the acupuncture techniques, all acupuncture will be performed by the same registered Chinese medicine practitioner. The patients will be treated in separated room or time to prevent communication between treatment group and placebo acupuncture group.

Method of randomization

The subjects will receive the Structured Clinical Interview for DSM-IV to evaluate psychiatric diagnoses and polysomnography to exclude specific sleep disorders prior to randomization. Block randomization is used in the randomization procedure. This is performed by using Excel to generate a randomized block list.16 Subjects are randomly assigned to one of the three groups after baseline visit.

Method of blinding

The subjects are told as follows “This study is to evaluate the therapeutic effects of acupuncture on treating insomnia in depressive patients. You will be randomly assigned to traditional acupuncture group for insomnia or acupuncture-like placebo treatment group”; “Traditional acupuncture is an acupuncture treatment that conventionally used in Chinese medicine practice; placebo acupuncture is a procedure which mimics the real acupuncture procedure and give you a perception that you are receiving the acupuncture treatment”. The researchers who analyse the data will be blind to the treatment allocation.

Concomitant Therapy

Antidepressants will be maintained the same dosage during the study period. Sedatives, hypnotics or anxiolytics are allowed during the study. The subjects are told to record their dosage of these medications. Drug counts will be conducted at each study visit. Individual psychotherapy should be maintained if it is ongoing prior to the study. Any new form of therapy or education is disallowed.

*Outcome Assessment*

Subjective assessment

1. Insomnia Severity Index (ISI) (Primary outcome measure)

ISI is a 7-item self-rating scale. The subjects rate their severity of sleep problem and the daytime function performance due to insomnia using a 5-point Likert scale.

2. Sleep log

The subjects record their daily sleep-wake schedule on a standardized sleep log.

3. Hamilton Depression Rating Scale (HDRS)

HDRS is a 21-item scale which the clinicians used to rate the severity of patients’ depression. HDRS rates the severity of other depressive symptoms such as low mood, insomnia, agitation, anxiety and weight-loss.

4. Pittsburgh Sleep Quality Index (PSQI)

PSQI is a self-rating scale that assesses the subjects’ sleep in the past month. It has seven components, namely subjective sleep quality, sleep latency, sleep duration, habitual sleep efficiency, sleep disturbance, use of sleeping medication, and daytime dysfunction.

5 Sheehan Disability Index (SDI)

SDI is a 3-item self-rating scale that assesses the subjects’ functioning regarding work/study, social life and family.

Objective assessment

Actigraph

Actigraph is a watch-like device used to estimate sleep-wake schedules by measurement of activity. The subjects are asked to wear the actigraph on the dominant wrists prior to light off for 3 consecutive nights. Subjects will be told to have usual bedtime when they are measured by actigraph.

Assessment for safety

Reason for withdrawal

When a subject withdraws before completing the study, the reason for withdrawal will be recorded.

Adverse events

Adverse events will be assessed at each visit. The researcher will ask using open-ended questions whether the subjects experience any adverse events during the assessment visit.

Assessment for credibility

Credibility of treatment rating scale (modified by C Vincent) will be used to assess the credibility of the treatments.17 The 4-item scale is specially designed to assess the credibility of acupuncture.

*Data Analysis*

Sample size estimation

Insomnia Severity Index (ISI) is selected as the primary outcome measure. The sample size estimation is based on our pilot study. We found that the SD of ISI score in the treatment and control group was 4.7 and 3.6, respectively, while the baseline and endpoint ISI score correlation coefficient was roughly 0.5. Vickers and Altman proposed that analysis of covariance (ANCOVA) was the preferred approach to analyse controlled trials with baseline and follow up measurements.18 We estimate the sample size requirement per treatment group using:

(1- ρ2)

An adjustment factor (1- ρ2) is used to determine the sample size in each group;19 and ρ is the baseline and endpoint measure correlation coefficient.

Let type I error a = 0.05; type II error β = 0.20; and power (1-β) = 80%. The SD δ1= 4.7, δ2 = 3.6 and ρ = 0.5. A clinically significant treatment effect is taken as a 3 ISI point between-group difference (Δ = 3). Therefore, a sample size of 23 is needed in each group. We estimate a 20% attrition rate; hence a sample size of around 30 in each group (90 in total) is planned for this study.

Data Management and Analysis

All data are double-entered and checked for consistency prior to analysis.

Baseline differences between the electroacupuncture, minimal and placebo acupuncture groups would be examined using unpaired t-test or χ2 test. The last observation carried forward method would be used to handle missing data. The outcome measures during acupuncture treatment and at posttreatment would be compared with that at baseline using paired t-test. A 2 × 3 (time × group) ANCOVA with baseline measure as a covariate would be used to investigate differences between the electroacupuncture, minimal and placebo acupuncture groups. Standardized effect size would be computed by dividing the difference in means by the pooled standard deviation to estimate treatment impact. The clinical significance of the interventions would be estimated by the proportion of participants who reached sleep-diary SOL or WASO of 30 minutes or less and SE of at least 85%, and χ2 or Fisher exact test would be used to test for group differences.

Safety analyses

Subjects who receive at least 1 acupuncture treatment will be included for safety analyses. Adverse events will be coded using the WHO Adverse Reaction Terminology Dictionary. Special attention will be given to those subjects who have discontinued treatment due to an adverse event or who experience a severe or serious adverse event.

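### The statement to subjects names two possible assignments, but the protocol randomises to three; it is false for the third of subjects sent to the waiting list

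*Protocol*

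**What the plan says.** Study Design, in the protocol's Plan of Investigation, sets out three arms: "Eligible patients will be randomized in a ratio of 1:1:1 to: (1) traditional electroacupuncture; (2) placebo acupuncture using Streitberger needle; and (3) waiting list control". It says of the third arm: "Patients in the waiting list control group will not receive any treatment for a period of 8 weeks after randomization". Those patients then receive the same treatment as the electroacupuncture group. Method of randomization repeats the number of arms: "Subjects are randomly assigned to one of the three groups after baseline visit".

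The next section, Method of blinding, gives in quotation marks what subjects are told: "You will be randomly assigned to traditional acupuncture group for insomnia or acupuncture-like placebo treatment group". The rest of that quoted text explains traditional acupuncture and placebo acupuncture. It mentions neither a waiting list nor a period without treatment, and it gives no allocation ratio.

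Two other statements bear on the point. The trial is presented as blinded to subjects without distinguishing the arms: "The proposed study is a randomized, prospective, placebo-controlled, single-blind trial of electroacupuncture for residual insomnia associated with MDD". Consent is required, under Subjects: "Written informed consent would be obtained prior to study procedure". The consent text itself is not in the material available for this review.

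**The concern.** The statement tells a subject which assignments are possible, and it leaves one out. A subject assigned to the waiting list gets something that the statement, on its face, did not allow for.

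This matters scientifically because of what the waiting list is for. Study Design aims to separate specific needling effects, expectation and other incidental effects, and background change such as regression to the mean. The waiting list is the only arm without a needling procedure, so it is the only reference for background change. The ISI, on which the sample size rests, is self-rated, and waiting-list subjects know that they are untreated. If they had been led to expect needling of one kind or the other, the surprise could affect how they rate their sleep and whether they stay in the trial.

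Missing values are to be filled by last observation carried forward (Data Management and Analysis). A subject who leaves on learning of the wait would therefore contribute an early value, possibly the baseline one, and any later spontaneous change in that subject would be lost.

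There is also the plain matter of giving subjects an accurate account of what they may be assigned to.

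**Working it through.** The point turns on comparing texts. The only arithmetic is the share of subjects concerned.

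**1. The plan's own sample size, which supplies the group size.** Inputs from Sample size estimation: SDs 4.7 and 3.6, correlation 0.5, difference 3 ISI points, and "Let type I error a = 0.05; type II error β = 0.20; and power (1-β) = 80"%. Sidedness is not stated; two-sided is assumed here.

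- Unadjusted: n = (1.960 + 0.842)² × (4.7² + 3.6²) / 3² = 7.849 × 35.05 / 9 = 30.57 per group.
- With the ANCOVA factor: 30.57 × (1 − 0.5²) = 30.57 × 0.75 = 22.93, so 23 per group, as the protocol states.
- With 20% attrition: 23 / 0.80 = 28.75, so 29, in line with the protocol's figure of around 30 per group and 90 in total.

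The sample size reproduces, and nothing in this point changes it.

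**2. Arms by section.**

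| Place in protocol | Electroacupuncture | Placebo acupuncture | Waiting list |
| --- | --- | --- | --- |
| Study Design | yes | yes | yes |
| Method of randomization | three groups, not named | three groups, not named | three groups, not named |
| Method of blinding, statement to subjects | yes | yes | no |

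The statement covers two of the three arms. No section describes a second statement or says that the waiting list is explained elsewhere.

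**3. Share of subjects concerned.** Under 1:1:1 the waiting list takes 1/3 of those randomised:

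- 90 / 3 = 30, using the total in Sample size estimation;
- 96 / 3 = 32, using the total in the synopsis.

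**4. Which comparisons are exposed.** Subjects in the two needled arms receive one of the two treatments that the statement named, so their assignment does not contradict what they heard. An effect of an unexpected assignment would arise in the waiting list, and so would enter electroacupuncture versus waiting list and placebo versus waiting list. Electroacupuncture versus placebo does not use that arm.

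**5. Size of any bias.** The protocol gives nothing from which to estimate it: no expected ISI shift from disappointment and no withdrawal rate specific to the waiting list. No figure is calculated here.

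**The case against.** The strongest reply is that the quoted text sits under Method of blinding and may be only the part of the disclosure that concerns masking. An untreated arm cannot be masked, so a section on masking would naturally deal with the two needled arms. The protocol does not say that these words are all that subjects hear, and written consent comes before any study procedure. This has force. A reader might infer that one third of subjects are never told of the waiting list, and the documents do not support that, because the consent form may disclose it. The objection does not rescue the sentence itself, which states what subjects may be assigned to and is wrong for this trial. If the consent form is correct, subjects receive two conflicting accounts.

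A reader might also infer that the statement promises a 1 in 2 chance of active treatment. It gives no ratio or probability, so that figure would be the reader's own. The chance of electroacupuncture at randomisation is 1/3. Because the waiting list later receives it too, the planned share eventually offered it is 1/3 + 1/3 = 2/3.

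Thirdly, disappointment is a hazard of any open waiting list with a self-rated outcome, even when subjects are fully informed, and here it may be softened by the treatment planned after 8 weeks. That stands. Only the part added by an inaccurate statement can be charged to the statement, and the documents offer no way to separate it. Setting an assumed shift, such as one ISI point, against the 3-point difference would have no basis in the protocol.

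**Conclusion.** The contradiction is explicit and should be corrected before enrolment: three arms are randomised, and the words given for subjects name two. The statement is false for the third of subjects assigned to the waiting list, 30 of 90 or 32 of 96. That conclusion rests only on the 1:1:1 ratio and on the statement being used as written.

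The consequence for the results is conditional. If the consent form also omits the waiting list, an unexpected allocation to waiting could alter withdrawal and self-rated ISI in that arm and bias comparisons with it. Worse ratings or lost spontaneous improvement would make acupuncture look better against the waiting list, but neither the direction nor the amount can be established from the protocol. If the consent form does disclose the waiting list, what remains is mainly an inconsistency to be put right. In either case electroacupuncture versus placebo is largely unaffected, and the sample size does not change.

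**What to change.** - Reword the statement in Method of blinding so that it names all three groups, the 1:1:1 ratio, the 8 weeks without study treatment in the waiting list, and the electroacupuncture that Study Design already provides for that group afterwards.
- Check the consent text against the new wording and bring the two into line if they differ.
- State in Study Design and Method of blinding that subject blinding applies only to electroacupuncture versus placebo, and that waiting-list subjects know their assignment.

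The cost is a rewording of the protocol, a matching change to the consent text if one is needed, and notification of the ethics committee. No patients, visits or changes to the analysis are required. The correction has to come before subjects are enrolled, because no later analysis can undo what they were told.
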